#### Secondary target group

The sample size of the secondary target group could not be deduced empirically. The number of members from the secondary target group will depend on the structural conditions of the nursing homes. In every nursing home, there must be a minimum of 6 individuals (MAKS-s therapists and other nursing staff) who meet the criteria for inclusion in the study.

### Recruitment strategies

Nursing homes from the postulated size in the recruitment areas are identified by means of their websites. Information material is sent to these nursing homes by post. Two weeks later, all the facilities that have been contacted are called by telephone and asked whether they are willing to participate. Cooperation contracts are signed with the nursing homes that are interested in participating in the study. After at least 24 nursing homes have signed a cooperation contract, recruitment will be completed.

### Eligibility of participants

All residents of the participating units in the 24 nursing homes will be included in the screening process. Additionally, in every nursing home, the members of the nursing and care staff who are involved most in the care of the participants of the study will be selected. The screening process will be conducted by trained nursing staff working in the participating nursing homes.

#### Primary target group

All residents will undergo a three-step standardised screening process to determine their suitability for the project. In the first step of the screening process, all residents fulfilling at least one of the following criteria are excluded: bedridden, blind, deaf, no sufficient knowledge of German, more than one stroke, severe depression, schizophrenia, an addictive disorder, concrete plan to leave the facility. In the second step, cognitive performance is assessed. Individuals who definitely have a MMSE (Mini-Mental State Examination) figure of over 9 points (estimated by the nursing staff) are excluded. Every other person is tested with the MMSE. Individuals who attain more than 9 points are excluded. All individuals who are potentially eligible to participate in the study are put on a list and randomised by a randomising list from our cooperation partner IMBE. After the randomisation, the nursing home staff apprise the legal representatives of the eligible individuals in the order of the randomisation list. After the legal representative provides written informed consent, the PWSD is included in the study. This process is performed until six people per nursing home give their consent.

#### Secondary target group

To select the individuals who are the most involved in the care of the participating PWSDs, three groups are formed. The first group consists of the therapists who will carry out the MAKS-s treatment. The second group is the nursing staff comprising the primary nurse and their stand in. The third group consists of the care staff involved in the occupational therapy of the study participants (in Germany, these are people who are trained to provide occupational therapy, but they are not nurses with degrees). The eligible nursing and care staff members are also informed about the study, and written informed consent is obtained from them.

### Intervention

The MAKS-s intervention is a multicomponent non-pharmacological intervention designed specifically for people with severe dementia. It consists of four components that are combined in the same order every day in a manualised intervention module lasting approximately 1 h. The participants have to use social skills in order to interact in a group. Social cooperation is promoted in all components.

#### The contents of the MAKS-s intervention

Table 3 provides an example of how the MAKS-s intervention is structured for 4 weeks. Due to the severe impairment of the PWSD, the 4-week plan can be repeated continuously. The daily treatment module begins with a social warm-up session, lasting approximately 10 min. Due to the amount of social contact in the group, the basic need for participation and social interaction is met. The social warm-up includes a welcome ritual, singing together, and some other recurring elements. The entire social warm-up is always conducted in the same order. Next is the sensorimotor session, which lasts about 20 min. The sensorimotor activation training meets the need for movement. After a motor ritual and a warm-up, exercises with handtools such as mini bean-bags or spiky massage balls are performed. Particular attention is paid to contracture prophylaxis and the training of motor skills that still remain as well as the promotion of body awareness. Subsequently, the cognitive session, lasting around 10 min, is performed. The cognitive stimulation conveys the feeling of success by addressing basic subconscious sensory memories. Due to cortical atrophia in severe dementia, higher cognitive processes cannot be addressed in PWSDs. Instead, rather unconscious processes such as priming or multisensory stimulation is used to activate any remaining long-term memory content, for example, well-known songs or poems. Those contents, despite the severity of the disease, can still be accessed via key stimuli (priming) because the corresponding regions in the cortex are less affected by Alzheimer’s Disease [29]. In particular, one area of the cortex that is less affected by Alzheimer’s dementia, the somatosensory cortex [29], which processes sensory impressions of tactile perception and depth sensitivity, is addressed by making people feel things with great tactile appeal. The last component performed in the MAKS-s intervention is the training in ADLs for about 20 min. Basic everyday activities such as putting lotion on one’s hands or cutting a piece of fruit are performed to promote gross and fine motor skills and especially procedural memory to maintain basic everyday skills. Thus, meaningful activity is experienced. (further examples are presented in Table 3, right column).

**Table 3 Tab3:** MAKS-s 4-week-plan

MAKS®-s 4-week-plan	Social warm-up session 10 min.	sensorimotor activation training 20 min.	cognitive stimulation 10 min	Training in acvtivities of daily living 20 min.
Monday 1	fixed ritual	throwing balls, mini-bean-bag	singing songs	fidget quilt
Wednesday 1	fixed ritual	playing football, twin-rubberball stick	sensory training	spreading bread
Friday 1	fixed ritual	marching, (spiky massage)balls	completing proverbs, poems, rhyms or fairy tales	washing hands
Monday 2	fixed ritual	throwing balls, mini-bean-bag	singing songs	fidget quilt
Wednesday 2	fixed ritual	Playing football, twin-rubberball stick	sensory training	Cutting fruits and eating with fork
Friday 2	fixed ritual	marching, (spiky massage)balls	completing proverbs, poems, rhyms or fairy tales	pinning and screwing
Monday 3	fixed ritual	throwing balls, mini-bean-bag	singing songs	fidget quilt
Wednesday 3	fixed ritual	Playing football, twin-rubberball stick	sensory training	spreading bread
Friday 3	fixed ritual	marching, (spiky massage)balls	completing proverbs, poems, rhyms or fairy tales	Nipping clothespins on towels
Monday 4	fixed ritual	throwing balls, mini-bean-bag	singing songs	fidget quilt
Wednesday 4	fixed ritual	Playing football, twin-rubberball stick	sensory training	peeling and cutting potatoes/eggs, eating with fork
Friday 4	fixed ritual	marching, (spiky massage)balls	completing proverbs, poems, rhyms or fairy tales	Free choice of activity

#### Implementation of the MAKS-s intervention

The nursing homes in the intervention group will commit themselves to carrying out the MAKS-s intervention in accordance with the manual every Monday, Wednesday, and Friday for 6 months. All study participants will participate in the intervention every day. MAKS-s will be carried out by two trained MAKS-s therapists, who have received 2 days of training. All materials used in the intervention will be given to the nursing homes in the intervention group at baseline and will be given to the control groups after the 6-month intervention period. Staff members at the study headquarters will be available to answer questions by phone or e-mail on weekdays. The project will not exert any influence over the pharmacological treatment of the participants or their individual participation in other activities. However, all these influences will be documented for all study participants. Due to findings from previous randomised-controlled trials, serious adverse events are not expected. Therefore, no stopping guidelines are necessary [10, 11].

### Measures

#### Primary outcome measures

*Neuropsychiatric inventory nursing home version (NPI-NH)* [30]*.* The NPI-NH, a deduction from the original Neuropsychiatric Inventory (NPI) [31], is a comprehensive retrospective observer rating scale for assessing the BPSD of individuals who reside in nursing homes by interviewing their formal caregivers. The NPI-NH evaluates 10 behavioural areas (delusions, hallucinations, agitation, depression, anxiety, apathy, irritability, euphoria, disinhibition, aberrant motor behaviour) and two types of neurovegetative changes (night-time behaviour disorders and appetite and eating abnormalities). The severity and frequency of each symptom are assessed by means of structured questions administered to formal caregivers. Multiplying the values of severity (1–3) and frequency (1–4) results in the score of the respective symptom, ranging from 0 to 12. The total NPI score ranges from 0 to 144 [32]. In addition, the impact of behavioural disturbances on formal caregivers can be scored by summarizing the occupational disruptiveness. The German version showed a moderate internal consistency of .55 and .68 (Cronbach’s α) and a relatively robust factor structure [32] confirming the results of studies from other countries [33, 34].

*QUALIDEM* [35, 36]*.* To measure Qol, the German version of the QUALIDEM is used [37]. The QUALIDEM is a dementia-specific Qol instrument that allows a retrospective proxy-based rating, assessed by formal caregivers to be applied in a residential setting. QUALIDEM consists of two consecutive versions that can be used in the different stages of dementia [38]. The version we will use in this study was developed for people with very severe dementia. It contains 18 items, categorised into six domains of Qol: care relationship (3 items), positive affect (4 items), negative affect (2 items), restless or tense behaviour (3 items), social relations (3 items), and social isolation (3 items). The response options for all items are “never”, “extremely rare”, “rarely,” “sometimes”, “often”, “frequently”, and “very frequently”, thereby resulting in an item score that ranges from 0 to 6. Higher scores indicate a higher QoL. The scores on the subscales are calculated by adding up the item scores [38]. The global score is calculated by adding up and transforming the subscale scores into values that can range from 0 to 100 (theoretical range) according to Dichter et al. [39]. The scores on the subscales yield a Qol profile [38]. Studies on validity have provided evidence of satisfactory construct validity [35, 40]. The application of a user guide results in a sufficient interrater reliability for the QUALIDEM subscales [37].

#### Secondary outcome measures

##### Primary target group

*Alzheimer’s Disease Cooperative Study Activities of Daily Living scale for Severe impairment (ADCS-ADL-sev)* [41]*.* The ADCS-ADL-sev is a questionnaire that is provided as an interview to the caregiver of the PWSD. It is a retrospective observer rating scale relating on the capability to execute one specific ADL, assessing the preceding 4 weeks. Each of the 19 items consists of a series of hierarchical questions. The possible answers range from total independence to total inability. The total point score ranges from 0 to 54, with higher scores indicating higher ADL performance.

The items from the original ADCS-ADL [42] scale were individually validated. A subset of 19 items met the criteria for applicability, reliability, good scaling, concordant validity, and sensitivity to detect change in performance over 6–12 months in PWSDs [41].

##### Secondary target group

*Professional Care Team Burden (PCTB) Scale* [43]*.* The PCTB is a self-rating scale for assessing the subjective burden of the professional care staff in nursing homes and other caregiving facilities. The measure contains 10 items divided into 3 subscales (structural burden, objective burden, subjective burden). The items are rated on a five-point scale ranging from strongly disagree to strongly agree. The total score ranges from 0 to 40 points, with lower values indicating higher burden.

The convergent validity was demonstrated by computing the correlation with the Perceived Stress Scale (PSS), indicating moderate to high validity [43]. Cronbach’s alpha for the complete scale was .79.

*Days spent unable to work*. The number of days spent unable to work by the nursing and care staff who are most involved in the care of the participating PWSDs will be recorded by the head of the nursing home.

#### Other measures

*Mini-Mental State Examination (MMSE)* [44]*.* The MMSE is the most popular screening test for dementia [45]. It evaluates five domains of cognitive abilities: orientation, registration, attention and calculation, recall, and language. The score ranges from 0 to 30 points, and 0 to 9 points indicates severe dementia.

*Sociodemographic data, personal and medical history, and comorbidity index.* The following data on each participant’s medical history will be collected by the nursing home staff at baseline: sociodemographic data (age, sex), level of care, medications, and diagnosis. Comorbidities are weighted using the updated and validated Charlson Comorbidity Index (CCI) [46]. It is used to calculate the effect of 12 medical diagnoses on the mortality rate. Higher scores indicate a higher 1-year mortality rate. The 1-year mortality increases from 12% (index = 0) to 85% (index ≥5). Validity and excellent reliability have been demonstrated in several studies [47, 48].

*Monitoring form.* During the 6-month intervention period, every change in the health situation of the PWSD will be documented: change in the level of care, change in medication, additional diagnosis, hospitalisation, absences, death, and retirement from the MAKS-s intervention (intervention group only).

*Evaluation of MAKS-s.* The implementation of the MAKS-s intervention will be documented by the MAKS-s therapists every week. The attendance of every participant of the study will be recorded, along with deviations from the manual in order to monitor the intensity and the quality of the MAKS-s intervention.

*Additional/other regular activities.* All other activities, such as individual care, basal stimulation, singing, gymnastics, arts and crafts and so on, will be documented by the care staff every week.

*Continuation of the MAKS-s intervention.* To get indications of sustainability of MAKS-s, 12 months after baseline, all nursing homes participating in the study will be interviewed about the implementation of the intervention. They will be asked about the frequency, duration, number of participants, and whether it is practical to incorporate into the everyday routine.

### Data collection

All data will be collected at the nursing homes. The variables referring to PWSD will be collected by psychology students who are employed and trained by the study headquarters. To reduce reporting bias, the formal care staff providing data on the PWSDs (NPI-NH, QUALIDEM, ADCS-ADL-sev) will not be involved in the MAKS-s intervention. Beyond this, the data collectors (trained students) will be blinded. The variables pertaining to the secondary target group will be collected by the contact people in the nursing homes. All data will be collected in written form. These data will be stored in a locked steel cabinet, and only the researchers involved in the MAKS-s study will have access to the data.

A pseudonym will be created for every member of the primary target group (PWSDs), and it cannot be retraced. The people in the secondary target group will give themselves a pseudonym.

### Data quality management

All individuals involved in the study are thoroughly trained in their specific task. The interviewers/testers undergo a 2-day training course on how to administer the questionnaires and follow the data collection guidelines. The contact people in the nursing homes receive 3 h of teaching on the study protocol, and the MAKS-s therapists receive 2 days of training on how to implement the intervention. If questions arise, the study headquarters can be contacted by phone or e-mail.

100% of the data will be checked for the completeness and correctness of the screening criteria, as part of the managing of data entry. We will also verify that informed consent was obtained from all participants or their legal representatives.

In order to ensure the quality of the data, a minimum of 5% of the data will be subject to a random audit. To obtain evidence of the interrater reliability, 5% of the QUALIDEM, the NPI-NH, and ADCS-ADL-sev will be collected from two different raters. Two nursing homes in the intervention group (15%) will be visited by the staff from the study headquarters to observe how the MAKS-s intervention is being conducted (treatment adherence). At the same time, we will check for the quality of the documentation (deviations from the manual) and the regular attendance of the study participants. The data received by the study headquarters will also be carefully checked for plausibility and inconsistencies. The data will be assessed for completeness. The same procedure will be applied to the follow-up data. After all data have been collected, the ranges of the items and the relationships between the variables will be checked for their plausibility.

### Analysis

#### Data analysis

In order to revise the quality of randomisation, the baseline data from the intervention and the control groups will be compared for statistically significant differences.

Descriptive statistics will be reported on all variables from the primary target group (PWSDs), such as age, sex, level of care, or Charlson Index, and from the secondary target group (formal caregivers), such as age, sex, or profession.

Hypotheses 1 to 3 will be tested by applying multiple regression analyses. To ensure the robustness of the results, both data analytic strategies “intention to treat” and “per protocol” will be applied. “Intention to treat” evaluations are carried out with all cases are still alive at the end of the intervention period.

Differences in days spent unable to work among the formal caregivers in the intervention group facilities compared with those in the control group (Hypothesis 4) will be tested for significance using the *t*-test for independent groups.

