## Methods/design

### Aims and hypotheses

The main aim of the MAKS-s study, which began in July 2019, is to find out whether a non-pharmacological intervention adapted to the special needs of PWSDs can reduce the BPSD of this target group (primary target group) and consequently improve their Qol. In addition, we expect that the intervention will enable the maintenance of basal activities of daily living (ADLs). There is also the possibility that this improvement will provide some relief for the formal caregivers (secondary target group), which will be shown in a reduction in the number of days spent unable to work.

Research hypotheses:

Based on the primary outcome:
I.By participating in MAKS-s, the BPSD and Qol of PWSDswill be significantly better in the intervention group than in the control group.

Based on the secondary outcome:
II.By participating in MAKS-s, the everyday practical skills of PWSDswill be significantly better in the intervention group than in the control group.III.In the care facilities in which MAKS-s is conducted, the dementia-related stress experience of the nursing and care staff (secondary target group) involved in the care of the participants will be significantly better in comparison with the nursing and care staff in the control facilities.IV.The assumed positive trend described in Hypothesis 3 will lead to a relevant reduction in the number of days spent unable to work for this group of individuals.

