### Study design and setting

A two-armed cluster-randomised, controlled, multicentre, prospective longitudinal study with a waitlist control group design will be conducted to test the abovementioned hypotheses.

The nursing homes are located in five areas (German federal state): Bavaria, Baden-Württemberg, Thuringia, Rhineland-Palatinate, and Saarland. All nursing homes (clusters) participating in the study will be randomly assigned to the intervention or control groups at baseline (through random selection) by our cooperation partner “Institut für Medizininformatik, Biometrie und Epidemiologie (IMBE)” at the Friedrich-Alexander University Erlangen-Nürnberg. The clusters will be allocated by applying a tree-step stratification process by using “protective versus non-protective ward”, “area”, and “nursing home size” in decreasing order to balance the structural parameters.

The contact people in each nursing home are trained by the study headquarters with respect to the study protocol, instruments, and screening procedure before randomisation. Informed consent from the legal representatives of the PWSDs and the nursing staff (i.e., trained nurses) and care staff (i.e., staff with no medical training) will also be obtained before randomisation. Nursing homes will be informed about their group assignment in written form by the study headquarters. In addition, the nursing homes in the intervention group will receive further training on the implementation of the MAKS-s intervention. This treatment will be performed through the 6-month intervention phase. The nursing homes in the control group will not carry out any specific treatment but will continue providing “care as usual”.

Because we are investigating a non-pharmacological intervention, not everybody participating in the study can be blinded. Due to the severity of dementia, we can assume that the PWSDs will be blind to the conditions of the study. The therapists performing the MAKS-s intervention cannot be blinded. The raters (nursing staff) will be “semi-blinded”. They will know about the group assignment but will have no knowledge of the intervention. The testers, who are trained students from the study headquarters, who will conduct the tests, will be completely blinded.

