### Sample size estimation

#### Primary target group

A power analysis was computed on the basis of the authors’ previous experience with the pilot study MAKS-s ([name]: Modification and implementation of the MAKS-aktiv! therapy with severrly demented people: a pilot experiment, unpublished master´s thesis, Friedrich-Alexander University Erlangen-Nürnberg). For this purpose, the effects of the subscales “mood”, “disturbing behaviour”, and “social behaviour” of the NOSGER (“Nurses’ Observation Scale for Geriatric Patients”) [27] were pooled. The result was an effect size of Cohen’s *d* = 0.52. The beta-error was set to four times the size of the alpha error (α = .05), as proposed by Cohen [28]. This resulted in a power of .80.

Under these conditions, an evaluation sample of 114 individuals (57 per group, 6 per nursing-home) was deemed necessary. On the basis of the previous MAKS study [10], we expect a drop-out rate (mainly caused by death or being bed-ridden) of 20% across 6 months. This means a total of 144 people with severe dementia has to be included in the study. To achieve this goal, only nursing homes with at least 40 residents are being included in the project. This could be deduced from the following considerations:
In nursing homes in Germany, 38.8% of residents suffer from severe dementia [1]. This means 15 out of 40 individuals.In the “MAKS aktiv” study, the rate of bedridden and/or blind/deaf residents was 26% [10]. In the group of severe dementia cases, this rate was 40%. This left 9 of the 15 people with severe dementia suitable for intervention.It can be assumed that at least 70% of the participants will be willing to participate after the legal representatives have been informed [10]. Thus, 6 of the 9 suitable PWSDs can be included in the study.

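### Homes are randomised, but the only method named for Hypotheses 1–3, both primary endpoints included, is single-level multiple regression with no stated allowance for homes

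*Protocol article*

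**What the plan says.** Study design and setting describes "A two-armed cluster-randomised, controlled, multicentre, prospective longitudinal study with a waitlist control group design" and fixes the unit of allocation: "All nursing homes (clusters) participating in the study will be randomly assigned to the intervention or control groups at baseline". Recruitment of homes ends once at least 24 have signed. Under Eligibility of participants, consent is sought until six residents per home are included. Sample size estimation requires at least six staff per home.

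The Data analysis section gives one sentence on the main tests: "Hypotheses 1 to 3 will be tested by applying multiple regression analyses". Hypothesis 1 holds both primary endpoints: "the BPSD and Qol of PWSDswill be significantly better in the intervention group than in the control group". Hypotheses 2 and 3 concern activities of daily living and staff burden. Hypothesis 4, on staff days unable to work, is to be examined with a *t*-"test for independent groups".

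No section mentions an intracluster correlation, a design effect, a random home effect, cluster-robust standard errors or an analysis of home means. Strengths and limitations explains why homes rather than residents were randomised (contamination and the staff outcome) but draws no consequence for the analysis.

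**The concern.** Residents of one home share staff and surroundings and, in the intervention arm, the same therapy group and therapists. Their outcomes may therefore be correlated. Treatment is assigned to the home, so the relevant error for the treatment contrast is the variation between homes. A regression on individual residents instead uses resident-level variation and counts every resident as a separate piece of evidence. If there is any positive correlation within homes, the standard error is too small.

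This affects both primary endpoints and two further hypotheses. A significant result could then reflect ordinary differences between homes more often than the nominal 5% allows, and the confidence intervals would be too narrow.

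**Working it through.** **1. Inputs.** From Sample size estimation: α = .05; "The result was an effect size of Cohen’s *d* = 0.52"; "This resulted in a power of .80"; 114 evaluable residents (57 per arm); 20% drop-out; 144 enrolled; at least six staff per home. From Recruitment strategies: at least 24 homes. Assumptions: two-sided test, exactly 24 homes, 12 per arm, and ICC from 0.01 to 0.20.

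**2. The plan's own figure.** For two independent groups, n per arm = 2(1.960 + 0.842)²/0.52² ≈ 58.1, so 59 per arm; the *t* version gives 60. The plan has 57. Power at 57 per arm is Φ(0.52 × √(57/2) − 1.960) = Φ(0.816) ≈ 79.3%, or 78.6% with the *t* distribution. A one-sided test would need only 46–47 per arm and does not fit. For drop-out, 114/0.8 = 142.5, so 143, and 24 × 6 = 144. The figure is thus close to an individually randomised calculation with a design effect of 1. It has no room for clustering.

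**3. Residents per home.** 114/24 = 4.75 evaluable. The sample-size sentence places six per home beside the evaluable total, but six is the number enrolled. The column for m = 6 below covers that reading and also the staff minimum.

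**4. Type I error of an unadjusted test.** Design effect DE = 1 + (m − 1) × ICC. True error = 2[1 − Φ(1.960/√DE)]. Unadjusted SE as a share of the correct SE = 1/√DE. Example with m = 4.75 and ICC 0.10: DE = 1 + 3.75 × 0.10 = 1.375; 1.960/√1.375 = 1.671; error = 9.5%; SE ratio = 0.85.

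| ICC (assumed) | DE, m = 4.75 | SE ratio | Error, m = 4.75 | Error, m = 6 |
|---|---|---|---|---|
| 0.01 | 1.038 | 0.98 | 5.4% | 5.6% |
| 0.02 | 1.075 | 0.96 | 5.9% | 6.2% |
| 0.05 | 1.188 | 0.92 | 7.2% | 8.0% |
| 0.10 | 1.375 | 0.85 | 9.5% | 11% |
| 0.20 | 1.750 | 0.76 | 13.8% | 16.6% |

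**5. Check by simulation.** 40,000 null trials per ICC were run with 24 homes (18 with five residents, six with four; 114 in all). The individual-level *t*-test rejected in 5.5%, 5.8%, 7.2%, 9.5% and 14.2% of trials at the five ICCs above, and in 5.0% at ICC 0. A *t*-test on home means stayed between 4.8% and 5.2% throughout.

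**6. Power under a valid analysis.** With 114 residents, d = 0.52 and 22 degrees of freedom (24 homes − 2), the non-centrality is 0.52 × √(57/(2 × DE)). Power is about 74% (ICC 0.01), 68% (0.05), 62% (0.10) and 52% (0.20).

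**The case against.** The strongest reply is that this is a condensed article. One sentence names a family of methods without model form, covariates or error structure. All analyses are to be supervised by a biometry institute, and a full analysis plan might add a home effect. A reader might infer that the plan declares homes to be ignored. It does not say so, and that part of the reply stands. Still, the article does not leave the method open: it names one that assumes independent observations. The sample size and the Hypothesis 4 test follow the same individual-level pattern. Supervision does not specify an analysis.

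A reader might also infer that a handful of nurses rate all residents of a home, so that shared raters add to the correlation. The article says only that raters are nursing or care staff not involved in the intervention. How many there are per home, and how residents are divided among them, is not stated. The point does not need it.

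A third reply is that allocation is stratified by ward type, area and home size, and that covariates in the regression could explain part of the between-home variation. This is fair: the figures above come from an unadjusted comparison with unstratified allocation, so the residual ICC could be lower than the raw one. Covariates do not, however, supply the correct error term for whatever correlation remains.

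Finally, 12 homes per arm is an assumption. Recruitment is to at least 24 homes, and Data quality management equates two intervention homes with 15%, which implies about 13 (2/0.15 = 13.3).

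**Conclusion.** The concern holds as a mismatch between the design and the only analysis named. For any positive ICC the direction is certain: standard errors too small and type I error above 5%. The size is not known, because the article gives no ICC. The excess is small at 0.01–0.02 (5.4–5.9% for residents), material from about 0.05 (7.2%) and large at 0.20 (about 14%). It is somewhat greater for Hypothesis 3 with six staff per home. At ICC 0 there is none. It would be too strong to say that the 5% level is exceeded whatever the data show, or that it is certainly exceeded by a large margin: either claim needs an ICC that the article does not provide. The figures rest on 24 homes split equally, 4.75 evaluable residents per home and a two-sided test. The matter should be settled before the outcome data are analysed, because it governs the test of both primary endpoints.

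**What to change.** In Data analysis, replace multiple regression for Hypotheses 1–3 with an analysis that respects the randomised homes. One suitable form is a linear mixed model with arm as a fixed effect, a random intercept for home and small-sample degrees of freedom. An equivalent home-level analysis, with degrees of freedom based on the number of homes, would serve as well. Report the estimated ICC for each outcome. Apply the same principle to Hypothesis 4, where a *t*-test on individual staff has the same weakness.

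The change is one of wording and needs no new data. Its cost is wider confidence intervals and power below the stated 80%: roughly 74% to 52% over ICCs of 0.01 to 0.20 with the planned 114 evaluable residents. That loss comes from the design, and single-level regression only hides it.
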